## 1. Introduction

Sports-related concussion (SRC) diagnosis is encumbered by a lack of validated, objective diagnostic tests [1]. Currently, the Sport Concussion Assessment Tool-5th edition (SCAT5) [2] is the standard instrument used to diagnose SRC at the side-line and pitch side of athletic and sporting events. However, research has suggested that exercise is a confounding variable not accounted for when using the SCAT5 [3,4]. This is concerning because the baseline SCAT5 is typically administered under resting conditions but is used to diagnose SRC following physical exertion during and after sports activity. In addition to the SCAT5, biochemical biomarkers have been suggested as objective markers to aid in SRC diagnosis. Similar to the SCAT5, potential SRC diagnostic biomarkers may also be confounded by exercise. Therefore, a particularly important goal of this study is to examine several biomechanical tests, motor control tests, and biomarkers to investigate whether they are influenced by contact in sports and the prevalence of injuries to the head. This will be achieved by investigating movement and coordination tests, cognitive tests, visual tests, and a variety of blood-based biomarkers prior to and after rugby match performance, with the specific aim of investigating performance degradation.

The blood-based biomarkers included in the analysis and evaluation will include protein S100B (S100B), creatine kinase (CK), cardiac troponin T (CTT), cortisol (C), neuron-specific enolase (NSE), brain-derived neurotrophic factor (BDNF), glial fibrillary acidic protein (GFAP), and ubiquitin carboxyl-terminal esterase L1 (UCHL1). Protein S100B has been shown to increase after a concussion [5,6,7], following punches and kicks to the head in boxing [8] and karate [9], after playing a contact sport [5,7,10,11,12,13,14,15,16,17,18,19,20,21], and after exercise [22,23,24,25,26,27,28]. Past research has shown that S100B can be used as a marker of brain injury since this protein is housed in the astrocytes; however, its ability to diagnose SRC appears to be confounded by exercise since S100B is also located in skeletal muscle [29]. Creatine kinase will be measured as an indicator of skeletal muscle damage [30] to aid in distinguishing S100B release caused by skeletal muscle injury.

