## 2. Materials and Methods

### 2.1. Study Design and Participant Recruitment

This study will be a randomized control trial. The study will consist of two groups: one sport-event group (SG) and one control group (CG); see Figure 1.

Sample sizes were calculated using G*Power 3.1 software (Heinrich-Heine-University Dusseldorf, Dusseldorf, Germany). Calculations were based on a previous study [7], and we aimed to achieve a substantial effect size of 0.8 (Cohen’s d) on blood biomarkers. With an alpha of 0.05 and a power of 80%, 40 participants (20 participants per group) are required to achieve a robust estimation of the relevant parameters. All participants will be required to be over 18 years of age to participate in the study. Prior to data collection, all participants will be fully familiarized with testing procedures and the laboratory environment. In addition, a pilot study will be performed prior to actual experimental data collection. This will provide valuable information concerning timing, standardization, subject preparation, data collection information, logistics, and experimental organization in terms of data management for all participants pre- and post-testing. Members of the research team supervising each different aspect of data collection will ensure the standardization and integrity of data collection. Blood samples will be collected at several phlebotomy locations to ensure bloodletting is performed immediately post-match. There will also be several locations provided by the research team to collect biomechanical and cognitive-motor task data. These multiple locations will enable efficiency and effectiveness in data collection post-event, minimizing the effect of time as a confounding variable.

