All the recruited participants will be male rugby 7 s players based at Cardiff Metropolitan University. Inclusion criteria will be participation in rugby 7 s tournaments for a minimum of 2 years and free from injury. After agreeing to participate in this study and passing the eligibility assessment, the participants will sign informed consent forms outlining the experimental design and procedures and will then be randomly assigned to SG or CG in a ratio of 1:1. The control group will comprise 7 s rugby players who are part of the 7 s squad but will not be participating in the actual rugby competition. Therefore, they will be injury- and fatigue-free, and direct comparisons will be possible to investigate the effect of games and contact on sports performance. In addition, baseline measures will also be useful in determining any changes within and between groups. This will enable meaningful comparisons between groups that are sport-specific. Both groups will participate in baseline and post-match data collection. Randomization will be conducted using the random function available in Excel software. All participants will be asked to maintain their regular training and dietary habits during the testing period. The participants will also be required to record their exercises and food intake for 24 h prior to each blood sampling. 

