### 2.5. Statistical Analysis

Data will be analyzed using IBM SPSS 26.0. Diagnostic testing (e.g., outlier detection, distribution examination, homogeneity checking) will be conducted for all data, and all skewed values and missing values will be addressed using a multiple imputation approach. To examine the differences between the baseline and the testing days for each of the physiological, cognitive-motor, and whole-body movement skills, a series of generalized linear mixed models will be employed, controlling for several demographic covariates. Post hoc tests will be performed using the Bonferroni procedure, Mann-Whitney U test, and Chi-square test for different types of data. The significance level will be set at 95% (two-tailed). The effect size of Cohen’s d will be calculated, with 0.3, 0.5, and 0.8 indicating small, medium, and large effect sizes, respectively.

Due to the difference in the type of data (discrete and continuous), a variety of methods will be employed, including statistical parameter mapping to examine continuous data between the four sessions and baseline. A canonical analysis will be used as a multivariate technique to determine the relationships between the variables and the selected performance of key dependent variables. All collected data will be anonymized and stored on a password-protected computer, with access only granted to the lead investigator.

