We expect a decline in coordination, cognitive-motor tasks, and whole-body mobility, owing to exhaustion and/or concussions, as the number of games increases. Concussive events and injuries will be assessed using a notational analysis recorded during each match. Specifically, a reduction in the performance variable associated with the mBESS stance and finger-to-nose task is expected. In the analysis of the emergent coordinative structures of the passing task, we expect to show a shift to a critical level, before which the outcome variable of passing accuracy will be maintained. Past this critical point, the self-organization of the biological structures will be unable to remain stable, and the coordination variability will rise above the functional level. Examining the structure and timing of these movement characteristics will allow us to link the dynamics to the evolving rugby games. Cognitive function tests, including the Pegboard, Tapping Task, Stroop word test, and reaction time task, are expected to display a reduction in outcomes in the repeated testing sessions as a result of fatigue and/or a concussive event. With respect to the blood-based biomarkers, we expect CK, cardiac troponin T, NSE, S100B, BDNF, GFAP, and UCHL1 to increase after a rugby match, as exercise and contact sports have been shown to cause these biomarkers to increase [8,9,10,11,12,13,14,15,16,17,18,19,20,21,22,23,24,25,26,27,28,35,37,44,45,46,47,48,49]. However, cortisol concentrations may not increase, as cortisol has been shown not to increase after American football play in the absence of brain injury [10,37]. Some variations in biomarker concentrations in the blood are expected to correspond to changes in biomechanical and cognitive-motor activities. In the examination of the interaction of whole-body movement, coordination testing, cognitive-motor tasks, and blood-based biomarkers, we expect to observe those variables most related to changes in the testing session and the other outcome variables, including the accuracy of passing.

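### The planned canonical analysis is too wide for 20 to 40 players unless the sets are kept small: raw canonical correlations are large under pure noise and cannot be read at face value

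*Protocol article*

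**What the plan says.** Section 2.5 (Statistical Analysis) of the protocol article commits to a named method: "A canonical analysis will be used as a multivariate technique to determine the relationships between the variables". The sentence goes on to describe the other side of the analysis as chosen performance on dependent variables, using the qualifiers *selected* and *key*. It is the only method in Section 2.5 described as relating variables to one another; the mixed models and the mapping of continuous data compare sessions with baseline.

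On how movement, coordination, cognition and biomarkers interact, the Discussion says: "we expect to observe those variables most related to changes in the testing session and the other outcome variables, including the accuracy of passing".

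The sample size in Section 2.1 was set for something else. The article says that "we aimed to achieve a substantial effect size of 0.8 (Cohen’s d) on blood biomarkers", and that "40 participants (20 participants per group) are required". No sample-size reasoning is given for a multivariate analysis. Also under Section 2.1, the control group does not take part in the competition, and testing takes place at baseline, after each of three games, and 24, 48 and 72 hours after the third.

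**The concern.** Canonical analysis searches for the weighted combination of one set of variables that correlates most highly with a weighted combination of the other. Because it maximises over all weights, the sample correlation is biased upward, and the bias is severe when the number of variables approaches the number of players. The weights then largely follow noise.

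At stake is the article's expectation of learning which variables go together across the three domains. A large first canonical correlation, and the variables with the largest weights, could be reported as evidence of linkage when a similar correlation would have appeared with no linkage. Two ways of organising the data would add false positives: stacking each player's sessions as if they were independent, and pooling players and controls so that a shared response to playing passes for a relation between variables.

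**Working it through.** **Inputs.** The Introduction names 8 biomarkers. Section 2.3.1 enumerates 5 whole-body tasks, and also 5 cognitive-motor tasks plus the MMSE, so 5 + 5 + 1 = 11 tasks. Several tasks give more than one score (the Pegboard has four subtests). Table 1 is shorter: 6 biomarkers and 4 whole-body tasks. The sample is 40, or 20 with match exposure. No dropout is assumed.

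**The plan's own figure.** For two means with d = 0.8 and 80% power, n per group = 2(z_alpha + z_power)²/d². One-sided: 2(1.645 + 0.842)²/0.64 = 19.3, so 20 per group. Two-sided: 2(1.960 + 0.842)²/0.64 = 24.5, so 25 per group. The stated 40 is thus reproduced with a one-sided test, while Section 2.5 is two-tailed; that is a separate matter. What matters here is that 40 comes from a mean difference, not from a relation between two sets.

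**Inflation under no relation.** Sample canonical correlations are the singular values of Qx′Qy, where Qx and Qy are orthonormal bases of the centred sets. Both sets were simulated as independent normal variables with all true correlations zero, in at least 2,000 data sets per case. Correlation within a set does not alter the result.

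| Set sizes | Mean first canonical correlation, n = 20 | n = 40 |
|---|---|---|
| 3 v 3 | 0.57 | 0.40 |
| 4 v 4 | 0.69 | 0.49 |
| 8 v 3 | 0.81 | 0.58 |
| 8 v 5 | 0.89 | 0.66 |
| 6 v 9 (Table 1 without the MMSE) | 0.94 | 0.71 |
| 8 v 11 | 0.996 | 0.80 |
| 8 v 15 | 1.00 | 0.87 |

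Two checks by hand. With 8 variables against 1, the expected squared multiple correlation under no relation is 8/(n − 1): 8/19 = 0.42 at n = 20 and 8/39 = 0.21 at n = 40, with square roots of 0.65 and 0.45. The simulated means were 0.63 and 0.45. For 8 v 11 at n = 20, centring leaves 19 dimensions and 8 + 11 = 19, so one more score forces a correlation of exactly 1.

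**Does a test rescue it?** For 8 v 11 with no relation and independent rows, at a nominal 5%:
- n = 20: rejection in 68% of runs (Bartlett chi-square) or 16% (Rao F).
- n = 40: 6–7% (Bartlett) or 4–5% (Rao F), which is close to nominal.
- Smaller sets at n = 20: the Rao F test also roughly holds its level.

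**Can the weights pick out the right variable?** One biomarker was related to one task with true correlation rho, in an 8 v 11 analysis. The largest biomarker weight fell on the right biomarker as follows (chance is 1/8 = 12.5%):

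| n | rho = 0.5 | rho = 0.7 |
|---|---|---|
| 20 | 19% | 30% |
| 40 | 46% | 86% |

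**Rows.**
- *Stacked sessions:* 7 per player, with an assumed within-player correlation of 0.5 and no relation. For 8 v 11, Rao's F rejected in 100% of runs with 20 or 40 players.
- *Pooled groups:* 40 players, no relation within groups, and an assumed shift of 0.8 SD on every variable (the article's biomarker effect size, extended to the tasks). Rao's F rejected in about 23–26% of runs for 8 v 11 and 8 v 5.

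**The case against.** The strongest reply is that nobody has said 8 biomarkers will face 11 tasks. The qualifiers *selected* and *key* suggest a subset, and listing the sets may reasonably be left to a statistical analysis plan. This stands. The 8 v 11 case is an assumption, and the absence of a list is not in itself the finding. The finding is that the stated method, with this number of players, gives inflated results even for modest sets.

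Three stronger readings are tempting, and the documents do not support them:
- *That correlations would be near-perfect throughout the range of 20 to 40 players.* This is true only for 20 players and nearly all variables. With 40 players and 8 v 11, the noise value is 0.80 and exceeds 0.9 in about 1% of runs. The article does not restrict the analysis to the sport group.
- *That the analysis cannot identify related variables at all.* With 40 independent rows the test roughly keeps its level, and a strong single relation (0.7) is found in 86% of runs.
- *That strong links would be reported by construction.* This assumes that raw coefficients are interpreted untested. Section 2.5 sets a significance level and nowhere says so.

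The reply also notes that the second aim and third hypothesis in the Introduction are worded as exploration, and that change over time is left to the mixed models. Both are right and limit how much rests on this analysis. The article also says only *a canonical analysis*; a version with one set coded by session or group is possible and was not simulated.

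**Conclusion.** The concern holds in a limited form. With 20 to 40 players, raw canonical correlations from this analysis cannot be taken at face value. Under no relation they average 0.69 (n = 20) or 0.49 (n = 40) for 4 v 4 variables, rising to 0.996 or 0.80 for 8 v 11. Ranking variables by their weights is unreliable in 20 players, and in 40 players unless the relation is strong. Ordinary tests are adequate on one row per player with 40 players, or with smaller sets in 20, but not for 8 v 11 in 20. They reject too often if sessions are stacked as independent or the group effect is left in.

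The figures assume normal variables, no dropout, and set sizes that the article does not state. The stacking and pooling figures also depend on the assumed within-player correlation of 0.5 and group shift of 0.8 SD.

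**What to change.** In Section 2.5, limit the canonical analysis to two small sets named in advance, for example 3 to 4 change scores each. Keep CK and S100B as separate variables, because the Introduction gives CK the role of helping to tell muscle-derived S100B apart; a single biomarker composite would lose that contrast. Use one row per player, and either remove the group effect or analyse the sport group alone. Since even 4 v 4 is inflated, report permutation p-values with players as the permuted unit, and leave-one-player-out canonical correlations in place of the raw ones. Label the analysis exploratory.

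Alternatively, replace it with a short pre-specified list of baseline-adjusted regressions, with 95% intervals and false-discovery-rate control.

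If a detectable correlation is stated, say what it refers to. By Fisher's z, r = tanh[(z_alpha + z_power)/√(n − 3)]. With 20 players and 80% power this is tanh[(1.960 + 0.842)/√17] = 0.59 for one unadjusted correlation, or tanh[(2.394 + 0.842)/√17] = 0.66 at alpha 0.05/3. Neither figure applies to the canonical analysis.

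The change is to the wording of the analysis and needs no new data. The price is that fewer variables are examined jointly.

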## 3. Discussion

Sports-related concussion (SRC) diagnosis is hindered by a lack of validated, objective diagnostic tests. There is an urgent requirement to understand and examine sports-related head trauma and the possible short-, medium-, and long-term consequences of a concussion. Using an interdisciplinary approach, this research will examine the changes in the blood-based biomarkers and biomechanical and cognitive-motor abilities of elite rugby players across a three-match tournament. The IMPACT Interdisciplinary Group’s purpose is to examine a number of functional biomechanical and motor control tests and biochemistry to investigate changes resulting from contact sports.

We expect a decline in coordination, cognitive-motor tasks, and whole-body mobility, owing to exhaustion and/or concussions, as the number of games increases. Concussive events and injuries will be assessed using a notational analysis recorded during each match. Specifically, a reduction in the performance variable associated with the mBESS stance and finger-to-nose task is expected. In the analysis of the emergent coordinative structures of the passing task, we expect to show a shift to a critical level, before which the outcome variable of passing accuracy will be maintained. Past this critical point, the self-organization of the biological structures will be unable to remain stable, and the coordination variability will rise above the functional level. Examining the structure and timing of these movement characteristics will allow us to link the dynamics to the evolving rugby games. Cognitive function tests, including the Pegboard, Tapping Task, Stroop word test, and reaction time task, are expected to display a reduction in outcomes in the repeated testing sessions as a result of fatigue and/or a concussive event. With respect to the blood-based biomarkers, we expect CK, cardiac troponin T, NSE, S100B, BDNF, GFAP, and UCHL1 to increase after a rugby match, as exercise and contact sports have been shown to cause these biomarkers to increase [8,9,10,11,12,13,14,15,16,17,18,19,20,21,22,23,24,25,26,27,28,35,37,44,45,46,47,48,49]. However, cortisol concentrations may not increase, as cortisol has been shown not to increase after American football play in the absence of brain injury [10,37]. Some variations in biomarker concentrations in the blood are expected to correspond to changes in biomechanical and cognitive-motor activities. In the examination of the interaction of whole-body movement, coordination testing, cognitive-motor tasks, and blood-based biomarkers, we expect to observe those variables most related to changes in the testing session and the other outcome variables, including the accuracy of passing.

The study proposed here will produce significant, validated research findings on the frequency of head trauma events and their impact on the performer’s biological system, with clear implications for doctors, scientists, and sports-regulating authorities. The implications of these findings will provide valid information that may result not only in a safer rugby environment but also in a shift in athleticism and a reconsideration of the rules of the game, with fewer impacts, collisions, and contact phases. Further implications may include the consideration of a technical fitness assessment after a concussive event. Players may be medically fit to return to play following injury, but skill levels may have deteriorated due to cognitive decline, resulting in the deterioration of cognitive abilities and skills. This suggestion may explain in part the reoccurrence of head injury linking concussive events to future concussive events. Therefore, medical examinations and comprehensive cognitive ability assessments may be required prior to returning to play. This study’s scope will be significant, and its consequences for health and well-being in athletic communities of all levels, genders, and ages will offer researchers a better knowledge of human responses to trauma. Through the dissemination of knowledge by publishing papers in international peer-reviewed journals, presenting at international conferences, and sharing our findings with the medical profession, governing bodies of sports, and coaches and trainers, the IMPACT group will provide meaningful information to drive the next generation of researchers investigating concussion in sports. Embracing an interdisciplinary approach allows a holistic view and novel conceptual understanding of this paradigm.

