Although cardiac troponin is typically used as an indicator of myocardial injury [31], it has also been shown to predict mortality rates from brain trauma in clinical environments [32,33,34]. Cardiac troponin will be investigated as a potential cardiovascular damage marker in rugby athletes. We expect minimal nonclinical elevations in cardiac troponin levels post-exercise as a result of exercise intensity and not cardiac pathology [35]. Cortisol is a biomarker related to stress that increases as a result of head injury [36] and also in response to head contact during boxing [8]. However, cortisol has not been shown to increase in contact sports in the absence of SRC [10,37]. Whether cortisol increases because of rugby play in the absence of SRC will be a partial focus of investigation in this study.

Neuron-specific enolase provides a diagnostic indication of brain trauma and has been shown to increase post-match in boxers [8,38], karate practitioners [9], soccer players [18,19], and American football players [10]. However, the use of NSE as a brain trauma biomarker has been questioned due to the absence of significant NSE increases in post-game hockey [20], as well as in concussed hockey players [12]. Measuring NSE pre- and post-rugby matches will help distinguish whether NSE consistently increases due to playing a contact sport in the absence of SRC. Furthermore, it is necessary to consider the implications of increased exercise on cognitive function and brain health.

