In order to understand the facets of motor control function that may underpin changes in the performance of gross motor skills, it is important to perform a number of tests of executive function and specific aspects of perception-action coupling. For example, reaction time is a promising indicator of visuo-motor deficits following SRC [65], which is quick and easy to quantify. Finger-tapping and fine motor skill tasks (f/e the Perdue Pegboard test) [66,67,68,69] have been used widely in cognitive psychology to identify neurological conditions. In order to understand the facets of motor control function that may underpin changes in the performance of gross motor skills, we will perform a number of perception-action and physical tasks. Specifically, we will explore reaction time, executive function (Stroop word test), and fine motor skills (finger tapping and Perdue Pegboard).

The study’s aim, therefore, is (1) to examine changes in biomarker concentrations and biomechanical and cognitive-motor abilities of elite rugby players across three-match tournaments until 72 h after the final game and (2) to explore the relationship between subconcussive head impacts and their intensity and changes in blood biomarker concentrations, biomechanical tasks, and cognitive-motor tasks.

It is hypothesized that (1) the whole-body movement, coordination, and cognitive-motor tasks will decrease significantly with the duration of games played because of fatigue and/or concussive events; (2) blood biomarkers (i.e., CK, cardiac troponin T, NSE, S100B, BDNF, GFAP, and UCHL1) will increase significantly after rugby tournaments; (3) a correlation will be explored between the number of head impacts (quantified with a notational analysis) and the aforementioned indicators. The study has been registered as a clinical trial (clinicaltrials.gov NCT04841876 (assessed on 16 March 2022)) and has been approved by the Research Ethics Committee of Hong Kong Baptist University (REC/20-21/0452).

All data collection, including motor control, biomechanics, and blood analyses, will be performed through formal collaboration with the universities constituting the Sport and Health Interdisciplinary Group in Movement & Performance from Acute & Chronic Head Trauma (IMPACT) research group based at Cardiff Metropolitan University. Funding for this project will be covered by the institutes involved.

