#### 2.3.2. Sports Performance Analysis

Sports performance analysis of training games will occur via computerized observation using a HUDL Elite software package (Version 11, SportsCode, Warriewood, NSW, Australia). This software will be used to create a workflow analyzing tactical and physical elements of performance, including collisions, impacts, and bouts of high-speed running (HSR). Collision measurement will occur after sessions and will be undertaken by two experienced performance analysts. The collision count will be deemed to include the sum count of all ball carries into contact, rucks, mauls, and, most importantly, tackles. All sessions will be recorded using a digital camera system.

Evidence-based preparation in elite rugby union has led to the increasing use of athlete tracking. External loads generated by the players will be calculated using accelerometers, local positioning systems (LPSs), global positioning systems (GPSs), and optical tracking systems [80]. Body load and impact measurements can be used to quantify the amount and intensity of any physical encounters and collisions between athletes, objects, or surfaces. Any serious injuries to the players during the three-game period will be managed immediately by the medical team.

Each player will wear a GPS micro-technology unit (mass = 67 g, 10 Hz V5.0 and 10 Hz S5, Catapult Innovations, Scoresby, VIC, Australia) in a pocket fitted in his/her playing jersey on the upper thoracic spine between the scapulae. Each GPS unit collects data at a rate of 10 hertz. The dependability of the device has already been proven to be valid and reliable for measuring speed and distance in team sports [81].

Because of their training and competitive routines, all players are completely familiar with the units. Throughout the data-collecting period, each player will wear the same assigned GPS unit. To ensure a comprehensive and high-quality satellite signal, GPS units will be turned on at least 10 min before the game. After the game, GPS data will be downloaded to a laptop and analyzed using Sprint 5.1 software (Catapult Innovations, Scoresby, VIC, Australia). Body load (measured in G-force) is the sum of all forces applied to an athlete, including acceleration/deceleration, related changes in direction, and impacts from both player-to-player and ground contact (foot strikes and falls) (Table 2).

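### Concussion is to be assessed by match notation, with no stated SRC classification, so the SRC-free biomarker questions and aim 2 on subconcussive impacts lack support from the stated procedure

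*Protocol article*

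**What the plan says.** Two questions in the Introduction (Section 1) depend on a player not having had SRC. On cortisol: "Whether cortisol increases because of rugby play in the absence of SRC will be a partial focus of investigation in this study". On NSE: "Measuring NSE pre- and post-rugby matches will help distinguish whether NSE consistently increases due to playing a contact sport in the absence of SRC". Aim 2, in the same section, is "to explore the relationship between subconcussive head impacts and their intensity and changes in blood biomarker concentrations", and it extends to the biomechanical and cognitive-motor tasks.

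The method for identifying concussion is given in Section 3 (Discussion): "Concussive events and injuries will be assessed using a notational analysis recorded during each match".

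Section 2.3.2 describes the match analysis. On who does it: "Collision measurement will occur after sessions and will be undertaken by two experienced performance analysts". On what is counted: "The collision count will be deemed to include the sum count of all ball carries into contact, rucks, mauls, and, most importantly, tackles". The same section names a wider workflow that also covers impacts and high-speed running. Hypothesis 3 says that head impacts are quantified by notation. Table 1 shows only placeholder letters for the notational variables.

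The medical team appears once, in Section 2.3.2: serious injuries "will be managed immediately by the medical team". Section 2.5 (Statistical Analysis) lists mixed models with demographic covariates, post hoc tests, statistical parameter mapping and canonical analysis. SRC status is not among the covariates, strata or exclusions it mentions.

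**The concern.** To say that a biomarker rises with rugby play but without SRC, or that it tracks subconcussive impacts, one must know which players had SRC and in which match. The article names a method for this, and the method it names is coding of play by performance analysts. A coder can record that a tackle or a head contact took place. Whether SRC followed is a clinical judgement, and the article describes no step at which that judgement is made or entered as data.

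A concussed player would therefore stay in the sport group without a label. His later sessions would be read as SRC-free exposure in the cortisol and NSE questions, and as part of a subconcussive dose-response in aim 2. Cortisol shows the difficulty most clearly. The Discussion expects that it may not rise after play without brain injury, and the Introduction says that it does rise after head injury. A rise in this study could then be a finding about rugby or an unlabelled concussion, and the planned data would not tell which.

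**Working it through.** **Inputs from the article.** 20 players per group, three matches, target effect d = 0.8, alpha 0.05, power 80% (Section 2.1); two-tailed testing (Section 2.5). The article gives no SRC rate and no size for the biomarker shift after SRC. Both are assumptions below.

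**The article's own figure.** n per group = 2(z for alpha + z for power)²/d².
- One-sided: 2(1.645 + 0.842)²/0.64 = 19.3, so 20 per group and 40 in total, as stated.
- Two-sided: 2(1.960 + 0.842)²/0.64 = 24.5, so 25 per group.

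The stated 40 thus fits a one-sided calculation. With 20 per group the exact two-sided t-test has 69.3% power. This point does not depend on that figure, which serves below only as the base for the cost of exclusions.

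**How likely is a case?** If all 20 sport-group players play all three matches there are 60 player-matches. P(at least one) = 1 − (1 − q)^60.
- Assumed q = 0.5% per player-match: 0.3 cases expected, P = 26%.
- Assumed q = 3%: 1.8 cases expected, P = 84%.

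**Effect on the group comparison.** With k unlabelled cases among 20, each shifted by D SD, the bias in the sport-minus-control mean is kD/20 SD.
- k = 1, D = 1 to 3: 0.05 to 0.15 SD.
- k = 2: 0.10 to 0.30 SD.
- k = 4: 0.20 to 0.60 SD.

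Simulation with no true effect (40,000 runs per setting, two-sided 5% t-test) gives these rejection rates:
- k = 1: about 5%, no rise.
- k = 2: 5.5 to 8%.
- k = 4: 8 to 23%.

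With one case, larger shifts do not raise the error rate either, because the outlier also widens the group SD. At 3, 5 and 10 SD the raw mean moves by 0.15, 0.25 and 0.50 SD, but the observed d averages only about 0.14, 0.20 and 0.27. Rejection stays at or below 5%, falling to about 1.7% at 10 SD.

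**Effect on aim 2.** Simulated correlation in 20 players, no true association, one concussed player (40,000 runs per setting):
- Exposure +2 SD, outcome shift 3 SD: mean spurious r = 0.24, false positives 14%.
- Exposure +2 SD, outcome shift 5 SD: mean r = 0.32, false positives 21 to 22%.
- Exposure +1 SD, shifts of 3 to 5 SD: mean r = 0.13 to 0.17, false positives do not rise.

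The aim 2 result is at risk when the concussed player is also among the most heavily exposed.

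**The case against.** The strongest reply has four parts.

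- **The formal aims are not conditioned on SRC.** Hypothesis 1 deliberately pools fatigue with concussive events. Hypothesis 2 concerns biomarkers after a tournament and does not list cortisol. For both, keeping a concussed player in the sport group is what the authors intend. This stands. The point is therefore limited to the cortisol and NSE questions, which are introductory framing, and to aim 2, which is exploratory.
- **The notation may be wider than the collision count.** A reader might infer that it codes nothing but carries, rucks, mauls and tackles. The article does not support that: the list defines the collision count only, and head impacts are also to be notated. This stands too. But a code for head contact, or even for a visible injury, still does not establish SRC.
- **Medical findings may be recorded elsewhere.** A reader might infer that the medical team's findings are not study data. The article does not say so, and a fuller protocol or SAP might include them. What remains is that the article states a method for assessing concussive events, and that method is notation.
- **Other measures could help.** SCAT5-type tasks, the MMSE, GFAP, UCHL1 and GPS impact zones are all collected, so it would be too strong to say that concussed players cannot be separated at all. But none of these is given a classifying role. The tasks and biomarkers are outcomes, so defining SRC from them would be circular for those outcomes. The GPS unit sits between the scapulae, and its body load includes foot strikes and falls.

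**Conclusion.** The concern holds in a limited form. The stated way of assessing concussion does not classify SRC. Conclusions about cortisol or NSE without SRC, and about subconcussive impacts in aim 2, are therefore not supported by the procedure as written. Hypotheses 1 and 2 are unaffected.

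A reader might infer that a single concussion could drive the sport-versus-control result. The figures do not support that: with one case the bias is probably small and false positives do not rise. Error rates in the group test grow only with several cases. The larger numerical risk lies in the aim 2 correlations, and only if the concussed player also has high exposure. All these sizes rest on assumed SRC rates, shifts and exposures. The gap in interpretation does not: whatever the rate, the article as it stands gives no basis for calling a player-session SRC-free.

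**What to change.** - Replace notation as the assessment of concussion with the match medical team's SRC decision, where one is made: suspected or diagnosed (yes/no), and in which match. Record it as a study variable, independently of the biomarker and task results.
- Restrict the SRC-free and aim 2 analyses to player-sessions before any recorded SRC. Report the all-player analysis, which fits hypotheses 1 and 2, alongside.
- Keep the notational count as the exposure measure only.

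**Cost.** One data field and one further analysis. Each player has six sessions after play begins (after games 1, 2 and 3, then 24, 48 and 72 h), so 20 × 6 = 120 in the sport group. One SRC removes six, five or four of them, depending on whether it occurs in match 1, 2 or 3: 3 to 5% of the total. If the player were dropped altogether, two-sided power at d = 0.8 would fall from 69.3% to 68.2% (66.9% for two players, 64.0% for four).

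**Downsides.** The clinical classification is imperfect, and the article itself notes that exercise confounds the standard SRC tool. It also depends on the team making such a decision, which the article does not state. The restricted analysis conditions on an event after randomization, so it should be labelled exploratory. The change affects what is recorded and analyzed, not how any player is managed.
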